### Aims

For this study, we will be comparing two distinct implementation strategies to support the uptake of IPV screening programs. First, all sites will receive a toolkit designed by the IPV Assistance Program, to be distributed to local staff responsible for encouraging IPV screening in primary care (toolkit plus implementation as usual [IAU]). Second, consistent with our stepped wedge design, during the study, each site will be assigned (in a staggered fashion) to cross over to more intensive implementation support in the form of implementation facilitation [31]. Implementation facilitation will entail external Office of Women’s Health Services experts working directly with the local primary care staff at participating sites to encourage IPV screening uptake and will also involve toolkit dissemination (toolkit plus implementation facilitation).

An additional aim of the study will be to compare two IPV screening tools. Specifically, a 5-item screener has been validated to detect probable IPV in primary care settings [9, 32], but feedback from the field to Women's Health Services leadership suggests the length of the 5-item screener may represent an implementation barrier in busy practices. Thus, as a secondary aim, we will compare the utility of the 5-item screener to a 1-item screener. Consistent with the RE-AIM Framework, the proposed research has the following specific aims:
Estimate the degree of reach, adoption, implementation fidelity, and maintenance achieved using two different implementation strategies (toolkit + IAU vs. toolkit + implementation facilitation) (implementation aim)Evaluate the clinical effectiveness of IPV screening programs, as evidenced by disclosure rates and post-screening psychosocial service use (i.e., social work and mental health services uptake) (clinical effectiveness aim)2a. Compare the clinical effectiveness of two IPV screening tools (5-item vs. 1-item screener) in terms of disclosure rates and post-screening psychosocial service useIdentify multi-level barriers to and facilitators of IPV screening program implementation and sustainment

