### Quantitative evaluation of the implementation outcomes

We propose to use RE-AIM as an evaluation framework to guide our qualitative analyses [30]. RE-AIM examines 5 dimensions: reach into the target population, effectiveness of the intervention, adoption by the setting, implementation fidelity, and maintenance (i.e., degree of sustainment over time). Of these, one (effectiveness of the intervention) pertains to clinical effectiveness (aim 2), while the remaining four relate to implementation (aims 1 and 3). Thus, RE-AIM is ideal for structuring the proposed hybrid implementation-effectiveness evaluation. Table 2 describes the specific outcome measures and data sources for each RE-AIM dimension. Given our hybrid type 2 design, we are equally interested in implementation and clinical effectiveness outcomes. For this program evaluation, our primary implementation outcome will be reach (i.e., the proportion of WVs eligible for IPV screening who receive the screening). Our primary clinical effectiveness outcome will be disclosure rates and post-screening psychosocial care use (i.e., the proportion of women with a positive IPV screen who accept a referral and use psychosocial services in the ensuing 2 months).

**Table 2 Tab2:** RE-AIM guides evaluation of the impact and clinical effectiveness of IPV screening programs

RE-AIM dimension (study aim)	Outcome measures	Numerator	Denominator	Data sources
Reach (aim 1): The proportion of eligible WVs receiving IPV screening program.	Proportion of WVs seen in primary care clinics during the last 3 months of each study phase who receive IPV screening	WVs who receive IPV screening as indicated by documentation (templated note, clinical reminder)	WVs seen in primary care clinics who are eligible for IPV screening (WVs seen in clinic with no screen in prior year)	VA Corporate Data Warehouse (CDW): IPV screening status from health factors in templated notes and clinical reminders
Effectiveness (aim 2): The clinical effectiveness of IPV screening programs on disclosure and post-screening psychosocial service use.	a. Proportion of eligible WVs who screen positive for IPV	a. WVs who screen positive for IPV	a. WVs who were screened for IPV	CDW: IPV screening status, responses, and referral disposition (accept or decline referrals) from health factors in note templates and clinical reminders; psychosocial service visits based on clinic stop codes

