	b. Proportion of WVs accepting psychosocial service referrals who use such services within 2 months	b. WVs who accepted referral and who use ≥ 1 psychosocial services within 2 months after positive screen	b. WVs who screen positive for IPV and accept a referral	
Adoption (aim 1): The absolute number/proportion of primary care clinics using the IPV screening program.	a. Proportion of primary care clinics completing IPV screening with at least 70% of eligible WVs during evaluation periods	a. Primary care clinics completing IPV screening with at least 70% of eligible WVs during evaluation periods	a. All primary care clinics who saw at least one WV eligible for IPV screening during evaluation periods	CDW: WV patient encounters within primary care clinics. IPV screening status from health factors in note templates and clinical reminders. IPV screening status, resource provision, and referrals offered determined by checkboxes as health factors in note templates and clinical reminders
	b. Proportion of primary care clinics delivering IPV screening program to at least 70% of eligible WVs during evaluation periods, including evidence of resource provision and referral offered for those with positive screens	b. Primary care clinics delivering the IPV screening program to at least 70% of eligible WVs during evaluation periods, including evidence of resource provision and referral offered for those with positive screens	b. All primary care clinics who saw at least one WV eligible for IPV screening during evaluation periods	
Implementation fidelity (aim 1): The extent to which IPV screening programs are conducted as intended by clinics.	Proportion of clinics for whom at least 60% of WVs accepting referrals attend psychosocial services within 2 months of positive screen Note: Additionally assessed via key informant interviews	Primary care clinics for whom at least 60% of WVs accepting referral attend 1 + psychosocial visits within the ensuing 2 months	All primary care clinics who referred at least one screen-positive WV to psychosocial services	CDW: IPV screening status, responses, and referral disposition (accept or decline referrals) from health factors in templated notes and clinical reminders; psychosocial service visits based on clinic stop codes

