Maintenance (aims 1 and 3): The degree to which IPV screening programs are sustained over time.	Repeat Reach analysis in last 3 months of study. Note: Implementation strategies and contextual factors impacting maintenance will be assessed via survey and key informant interviews	Same as Reach analysis above, but with data collection occurring 9–12 months after IF ends	Same as Reach analysis above, but with data collection occurring 9–12 months after IF ends	CDW: For repeat of Reach analysis

We will extract relevant administrative and clinical data for all VAMCs from the VA Corporate Data Warehouse (CDW) for all five dimensions of RE-AIM (see Table 1 below for details). The templated note or clinical reminder is required for the study and includes health factors for IPV screening (i.e., disclosure), response (i.e., resources provided), and referrals offered (i.e., accepted or declined IPV Assistance Program-Coordinator referral; accepted or declined psychosocial services referral). Psychosocial care use, and time to first post-screening psychosocial care use, also come from CDW based on clinic stop codes for social work, psychology, psychiatry, primary care mental health integration, drug or alcohol treatment, and housing services.

Our operation partners are interested in testing whether a brief 1-item screener can be as effective as a more comprehensive (but lengthier) 5-item screener a modified Hurt, Insult, Threaten, Scream tool [40], which has been validated for use with the WV population [9, 32]. The tool asks individuals to indicate how often in the past year a current or past partner has done any of the following: “insulted or talked down to you,” “screamed or cursed at you,” “threatened you with harm,” “physically hurt you,” or “pressured or forced you to have sexual activities.” Response options for each item ranges from 1 (never) to 5 (frequently). Endorsement of any item indicates a positive screen. A more efficient screening tool could potentially enhance the uptake of IPV screening programs. However, prior to formal adoption of a 1-item tool, it is critical to evaluate the effectiveness of the tool in eliciting IPV disclosures (sub-aim 2a). The item was developed by a panel of IPV and women’s health clinical experts and researchers and consists of “In the past 12 months, have you experienced insulting, screaming, threatening, hitting, or unwanted sexual activity by a former or current partner?”

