We will repeat these analyses to compare the clinical effectiveness of the 5-item tool and 1-item tool as well. To evaluate the extent to which IPV screening programs facilitate timely access to psychosocial services, we compare the median number of days to first new psychosocial service visits following a positive screen for women who accepted referrals during and after the IF + toolkit implementation period. In sum, our GEE analyses will allow us to determine the extent to which changes in the quantitative outcome measures described in Table 2 prior to the implementation facilitation differ along two dimensions: (1) based on the changes during and after the implementation period and (2) based on the use of the 5-item vs. 1-item screener.

We will supplement these quantitative data, derived from the CDW, with a 50-item electronic survey to all internal facilitators at pre-facilitation, post-facilitation, and the sustainment phases to assess the use of discrete implementation strategies at each site during each study period. The survey assesses 50 of the 73 strategies described by the Expert Recommendations for Implementing Change (ERIC) study [44], which has shown validity when strategies are assessed via survey [45]. To reduce participant burden, only the 50 strategies most germane to the IPV screening program implementation are queried (i.e., excluded financial incentives as this is irrelevant in VA) and we also inquire about the perceived effectiveness of each strategy on a Likert-type scale. The responses will inform a deeper dive into the use and perceived effectiveness of implementation strategies in subsequent internal facilitator interviews (see Qualitative evaluation of the implementation outcomes and adaptations made to IPV screening programs section).

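### Sub-aim 2a compares service use only among women each screener itself flagged, so the service-use half of the comparison is not like for like

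*Protocol article*

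**What the plan says.** The Aims section sets sub-aim 2a as: "Compare the clinical effectiveness of two IPV screening tools (5-item vs. 1-item screener) in terms of disclosure rates and post-screening psychosocial service" use. Under Stepped wedge trial design, the screener is assigned to sites within each wave, so a woman is classified by one tool only.

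The section Quantitative evaluation of the implementation outcomes gives the method: "We will repeat these analyses to compare the clinical effectiveness of the 5-item tool and 1-item tool as well". The outcomes being repeated are those of Table 2, Effectiveness:

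- Outcome a (disclosure) has as denominator "a. WVs who were screened for IPV".
- Outcome b (service use) has as numerator "b. WVs who accepted referral and who use ≥ 1 psychosocial services within 2 months after positive screen" and as denominator "b. WVs who screen positive for IPV and accept a referral".

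The text of the same section defines service use as "the proportion of women with a positive IPV screen who accept a referral and use psychosocial services in the ensuing 2 months", which can be read as having all screen-positive women as denominator. The time-to-first-visit comparison is also limited to women with a positive screen who accepted a referral. No service-use outcome has all screened women as denominator.

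For the 5-item tool, "Endorsement of any item indicates a positive screen", with each behaviour rated on a five-point frequency scale. The 1-item tool is one compound question that names insulting, screaming, threatening, hitting and unwanted sexual activity.

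**The concern.** Assigning screeners to sites through the balancing algorithm aims to make the women screened with each tool comparable. A positive screen, and the acceptance that follows it, come after assignment and depend on the tool. Restricting the comparison to those women gives up the comparability that the assignment was meant to secure: it compares the 5-item tool's positives with the 1-item tool's positives, and these need not be the same kind of women.

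The patient-level covariates named for the GEE models (age, mental health diagnoses, recent psychosocial service use) do not include severity of violence. As worded, the 1-item tool yields no per-behaviour frequency scores from which severity could be adjusted for.

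At stake is the reading of one of the two measures named for sub-aim 2a. The operational partners want to know whether the shorter tool is as effective as the longer one. A service-use rate that differs only because the tools select different women does not answer that.

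**Working it through.** **The plan's own figure.** The Power analyses section states power above 90% for post-screening psychosocial visits at 5% type I error. It gives no rates, numbers of women, intraclass correlation or effect size, so the figure can be neither reproduced nor refuted. The point does not depend on it.

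**Inputs.** From the document: past-year prevalence of 19% (Background), that is 190 cases per 1000 screened. Everything else is assumed: no false positives; both tools detect 95% of severe cases; tool A detects 90% of milder cases and tool B fewer. A and B are labels only; the document does not say which screener, if either, is B.

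**Formulas**, summed over severe and milder cases:

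- positives = cases × sensitivity
- acceptors = positives × acceptance
- users = acceptors × use after acceptance

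**One case worked through.** Assume 40% of cases are severe (76 severe, 114 milder), acceptance 50% severe and 20% milder, use after acceptance 70% severe and 40% milder, and tool B detecting 60% of milder cases.

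- Tool A: positives 72.2 + 102.6 = 174.8; acceptors 36.1 + 20.5 = 56.6; users 25.3 + 8.2 = 33.5.
- Tool B: positives 72.2 + 68.4 = 140.6; acceptors 36.1 + 13.7 = 49.8; users 25.3 + 5.5 = 30.7.

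| Measure | Tool A | Tool B |
|---|---|---|
| Disclosure (positives / screened) | 17.5% | 14.1% |
| Table 2b (users / acceptors) | 59.1% | 61.8% |
| Text reading (users / positives) | 19.2% | 21.9% |
| Users / screened | 3.35% | 3.07% |

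Tool B looks better on both conditional measures, yet links 2.7 fewer women per 1000, a loss of 2.74 / 33.48 = 8%.

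**Range.** The grid used a severe share of 30%, 40% or 50%; tool B sensitivity to milder cases of 80%, 60% or 40%; and three rate sets (acceptance severe/milder; use severe/milder): 50/20 and 70/40, 50/30 and 60/50, 50/50 and 70/40.

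- Table 2b favours B by 0.3 to 6.0 points.
- The text reading favours B by 0.4 to 5.4 points.
- The loss of users per 1000 is milder cases × fall in sensitivity × acceptance × use. The smallest is 95 × 0.10 × 0.20 × 0.40 = 0.76; the largest is 133 × 0.50 × 0.50 × 0.40 = 13.3.

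**No severity gradient.** With 40% acceptance and 60% use in both groups, the conditional measures tie at 60.0% and 24.0% for every sensitivity. The loss is still between 95 × 0.10 × 0.24 = 2.3 and 133 × 0.50 × 0.24 = 16.0 women per 1000.

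**The case against.** The strongest reply is that sub-aim 2a does not rest on service use alone. Disclosure is compared per woman screened, a denominator that the tool does not select, and the article ties formal adoption of the 1-item tool specifically to its effectiveness in eliciting disclosures. In the worked case disclosure falls from 17.5% to 14.1%. This stands. A reader might infer that the plan would let a less sensitive tool be adopted unnoticed; the document does not support that.

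A reader might also infer that the 1-item tool is the one that misses milder cases, since the 5-item tool is positive on any single endorsement. The article gives no sensitivity for either tool, and the 1-item question also asks about insults. A large loss can be produced by assuming a wide detection gap, but nothing in the document supports a particular gap. The lower service use among milder cases, needed for the conditional rate to favour the less sensitive tool, is likewise an assumption.

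It can further be said that the yield is recoverable from planned data. Under the text reading it is the product of two planned proportions (17.48% × 19.15% = 3.35%). Under Table 2b it also needs acceptance among positives, which is extracted but is not a Table 2 effectiveness outcome. This shows that the remedy is cheap. It does not make the conditional proportion a fair comparison, and no between-tool analysis of the yield is stated.

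Follow-through among women who accept a referral is a legitimate linkage measure, and the screener comparison is a secondary aim. Both are right, and they argue against demoting the planned outcome or setting an adoption rule on disclosure and yield alone. Such a rule would leave out reach, although easier uptake is the rationale for the shorter tool.

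**Conclusion.** The point holds for the service-use half of sub-aim 2a and no further. Under either denominator, service use is conditional on the result of the tool being compared, and the named covariates do not restore comparability. The conditional proportion can therefore favour a tool that links fewer women, or tie when one tool links fewer.

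Direction and size in this trial are unknown. The ranges in the working illustrate what the outcome definition allows and are not predictions. The reversal requires that one tool detects fewer milder cases and that those women accept or use services less often. The failure to show a loss needs only the first condition.

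This is an outcome definition that the article fixes in Table 2, not a detail left to an analysis plan. It should be changed, but it does not undermine the disclosure comparison.

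**What to change.** For sub-aim 2a, define the between-tool service-use comparison as the number of women who screen positive, accept a referral and use at least one psychosocial service within 2 months, divided by all women screened with that tool. Use the same GEE model and the same Corporate Data Warehouse fields.

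Keep the conditional proportion as a linkage measure reported alongside, with its denominator reconciled between the text and Table 2, and state that it is not a like-for-like comparison of the tools. Interpret both together with disclosure and reach.

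The cost is the wording of one outcome; no new data are needed. There are two downsides. The yield is a smaller proportion than the conditional rate (about 3% against about 60% in the worked case). It can also rise with false positives, or with service use that would have occurred anyway, since visits are counted from broad clinic stop codes. Both should be stated when it is reported.

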**Methods/design:**

This paper describes the planned evaluation of VA’s nationwide implementation of IPV screening programs in primary care clinics through a randomized implementation-effectiveness hybrid type 2 trial. With the support of our VA operational partners, we propose a stepped wedge design to compare the impact of two implementation strategies of differing intensities (toolkit + implementation as usual vs. toolkit + implementation facilitation) and investigate the clinical effectiveness of IPV screening programs. Using balanced randomization, 16–20 VA Medical Centers will be assigned to receive implementation facilitation in one of three waves, with implementation support lasting 6 months. Implementation facilitation in this effort consists of the coordinated efforts of the two types of facilitators, external and internal. Implementation facilitation is compared to dissemination of a toolkit plus implementation as usual. We propose a mixed methods approach to collect quantitative (clinical records data) and qualitative (key informant interviews) implementation outcomes, as well as quantitative (clinical records data) clinical effectiveness outcomes. We will supplement these data collection methods with provider surveys to assess discrete implementation strategies used before, during, and following implementation facilitation. The integrated-Promoting Action on Research Implementation in Health Services (i-PARIHS) framework will guide the qualitative data collection and analysis. Summative data will be analyzed using the Reach Effectiveness Adoption Implementation Maintenance (RE-AIM) framework.

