### Stepped wedge trial design

We will use a stepped wedge controlled trial design [33], such that all sites will start with the less intensive implementation strategies (toolkit + IAU) before receiving the more intensive implementation support (toolkit + implementation facilitation) in a staggered fashion (Fig. 1). Stepped wedge designs have their roots in balanced incomplete block designs [34]. A stepped wedge has the advantage of minimizing burden on implementation support personnel as start times are staggered, with all sites ultimately receiving the implementation facilitation strategy. We aim to recruit 16–20 VA Medical Centers (VAMCs) as sites, with about six sites assigned to each of the three waves with start times staggered by 6-month intervals. All sites will start with 3 months in the less-intensive toolkit + IAU condition to allow the collection of baseline data. When each site switches to the more intensive intervention, they will receive 6 months of active implementation facilitation followed by 6 months of step-down.

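### The median-days-to-first-visit analysis has no toolkit + IAU comparator, so it cannot show whether access became faster than under the control condition

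*Protocol article*

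**What the plan says.** All of this is in the Protocol article.

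- **Purpose.** Quantitative evaluation of the implementation outcomes: "To evaluate the extent to which IPV screening programs facilitate timely access to psychosocial services".
- **Statistic.** Same sentence: "we compare the median number of days to first new psychosocial service visits following a positive screen".
- **Women and periods.** Same sentence: "women who accepted referrals during and after the IF + toolkit implementation period".
- **Data source.** Psychosocial care use and "time to first post-screening psychosocial care use, also come from CDW based on clinic stop codes". Nothing limits these data to the facilitation period.
- **The trial's contrast.** Abstract, Methods/design: "Implementation facilitation is compared to dissemination of a toolkit plus implementation as usual".
- **Control time.** Stepped wedge trial design: "All sites will start with 3 months in the less-intensive toolkit + IAU condition to allow the collection of baseline data".
- **Summing-up sentence.** The GEE analyses are to show how "changes in the quantitative outcome measures described in Table 2 prior to the implementation facilitation differ along two dimensions", the two being change during and after the implementation period, and screener type.
- **Related access outcome.** Table 2, effectiveness outcome b, has as numerator "WVs who accepted referral and who use ≥ 1 psychosocial services within 2 months after positive screen". Its denominator is all women who screened positive and accepted a referral.

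**The concern.** The sentence asks whether access is timely and then compares, or pools, two periods that both come after a site has crossed over. The trial exists to compare facilitation with toolkit + IAU, and every site spends time in IAU before crossing over, yet this analysis leaves that time out.

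A difference between the during and after periods says whether speed held up once active support ended. It does not say whether speed improved. If facilitation shortened the wait and the gain lasted, the planned comparison would return nothing, and a reader could take that as no effect on timeliness. If the wait lengthened after support ended, it could still be shorter than under IAU, or it could be longer; the analysis could not tell which. This is the only analysis of speed of access that the article describes.

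**Working it through.** The article gives no effect size, sample size or power for median days, so there is no figure to reproduce. The check is a comparison of the text, followed by an illustration with assumed values.

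**1. Does any reading include IAU?** The sentence can be read two ways.

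- *During versus after facilitation.* Both groups are post-crossover, so there is no IAU group.
- *Women from both periods pooled and compared by screener.* The preceding sentence concerns the 5-item and 1-item tools, so this is possible. Again there is no IAU group.

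**2. Does the summing-up sentence supply one?** It names a pre-facilitation period, but only for measures in Table 2. Those are reach, effectiveness a and b, adoption a and b, fidelity and maintenance. All are proportions with a numerator and a denominator, to be analysed by logistic regression. Time to first visit is not among them, so the sentence does not reach it.

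**3. Are IAU data available?** Each site has at least 3 months of IAU. If all sites start together and waves are 6 months apart, IAU time is about 3, 3 + 6 = 9 and 9 + 6 = 15 months for waves 1, 2 and 3. The toolkit, with its note templates, goes to all sites at the outset; the template or reminder is required for the study; and visit timing comes from Corporate Data Warehouse (CDW) stop codes.

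**4. What the planned contrast can show.** For any measure of speed,

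IAU − after = (IAU − during) + (during − after).

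Read as during versus after, the plan estimates only the last term. That term is zero whenever speed is the same in the two periods, whatever it was under IAU.

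**5. Illustration (all inputs assumed).** Let a share π of acceptors ever attend, with exponential waits of mean m among attenders.

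- Median among attenders: m × ln 2.
- Median over all acceptors: solve π(1 − e^(−t/m)) = 0.5, giving t = −m × ln(1 − 0.5/π). It is not reached if π ≤ 0.5.

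Take m = 30 days under IAU and 20 days both during and after facilitation.

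| Median days | IAU | During | After | During − after | IAU − during |
|---|---|---|---|---|---|
| Attenders | 20.8 | 13.9 | 13.9 | 0 | 6.9 |
| All acceptors, π = 0.8 | 29.4 | 19.6 | 19.6 | 0 | 9.8 |
| All acceptors, π = 0.6 | 53.8 | 35.8 | 35.8 | 0 | 17.9 |

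(Differences are taken before rounding.) For example, 30 × ln 2 = 20.8, and −20 × ln(1 − 0.5/0.6) = 35.8. The planned contrast is zero in every row, while the contrast with control runs from 6.9 to 17.9 days. The zero follows from equal waits in the two periods and does not depend on the exponential form.

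**The case against.** **Access is already measured against the pre-facilitation period.** This stands. Outcome b counts every acceptor, so women who do not attend within 2 months count as failures, and post-screening service use is part of the primary clinical effectiveness outcome. A reader might infer that the plan cannot show improved access at all; it can, as attendance within 2 months. What it lacks is a controlled comparison of how quickly women attend.

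**Women who never attend.** A reader might infer that they are dropped, since days to a visit are undefined without one. The article does not say so. It defines the population by acceptance of a referral, not by attendance, and a Kaplan-Meier median over all acceptors fits the same words. Censoring rules are commonly left to a fuller document. This is silence, not a misstatement.

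**Calendar time.** A reader might also infer that the comparison ignores it. The article says its GEE analyses address the study aims while controlling for site characteristics and calendar time, and it names no model for the median. Again this is silence.

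**The question is about screening programs, not facilitation.** There is force in this. Women screened and referred under IAU also received screening and referral, so IAU versus facilitation compares implementation strategies. But a during-versus-after or between-screener comparison does not contrast screening with its absence either, and the strategy contrast is the one the trial was built to make.

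**Conclusion.** The point holds for the comparator and for nothing wider. As written, the median-days analysis includes no toolkit + IAU group on either reading, so it cannot show whether access became faster than under control, and a lasting gain would appear as no difference. The size cannot be taken from the article; under the assumed means of 30 and 20 days, a true difference of 6.9 to 17.9 days is invisible to a during-versus-after comparison. This is a supplementary measure outside Table 2, and the primary outcomes are unaffected. The conclusion rests on the wording of one sentence, and on the summing-up sentence applying only to the Table 2 measures that it names.

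**What to change.** State the contrast as toolkit + IAU versus during versus after facilitation, using the same CDW fields, with the site and calendar-time control already planned for the GEE models. If a comparison by screener is also meant, say so separately.

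Analyse time from positive screen to first new psychosocial visit among all women who accepted a referral, censored at a common horizon such as the plan's own 2 months, so that women with no visit stay in the analysis. Report cumulative attendance curves by period, since a median is not reached if fewer than half attend by the horizon. A time-to-event model that allows for clustering by medical center and includes calendar-period terms would serve.

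The cost is a change of wording, with no new data collection. Screening may be uncommon under IAU, so that group may be small and its interval wide; this should be reported and is no reason to leave the comparator out. The result should be described as a comparison of implementation strategies, not of screening with no screening.
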